## Abstract

**Background:**

The prevalence of cancer increases every year, leading to a growing population of patients and survivors in need for care. To achieve good quality care, a patient-centered approach is essential. Correct and timely detection of needs throughout the different stages of the care trajectory is crucial and can be supported by the use of screening and assessment in a stepped-care approach. The Cancer Rehabilitation Evaluation System (CARES) is a valuable and comprehensive quality of life and needs assessment instrument. For use in Flemish research and clinical practice, the CARES tool was translated for the Dutch-speaking part of Belgium (Flanders) from its original English format. This protocol paper describes the translation and revalidation of this Flemish CARES version.

**Methods:**

After forward-backward translation of the CARES into Flemish we aim to recruit 150 adult cancer patients with a primary cancer diagnosis (stage I, II or III) for validation. In this study with a combination of qualitative and a quantitative approach, qualitative data will be collected through focus groups and supplemented by two phases of quantitative data collection: i) an initial patient survey containing questions on socio-demographic and medical data, the CARES and seven concurrent instruments; and ii) a second survey administered after 1 week containing the CARES and supplementary questions to explore their impressions on the content and the feasibility of the CARES.

**Discussion:**

With this extensive data collection process, psychometric validity of the Flemish CARES can be tested thoroughly using classical test theory. Internal consistency of summary scales, test-retest reliability, content validity, construct validity, concurrent validity and feasibility of the instrument will be examined. If the Flemish CARES version is found reliable, valid and feasible, it will be used in future research and clinical practice. Comprehensive assessment with the CARES in a stepped-care approach can facilitate timely identification of cancer patients’ psychosocial concerns and care needs so it can contribute to efficient provision of patient-centered quality care.

**Trial registration:**

ClinicalTrials.gov: NCT02282696 (July 16, 2014).

**Electronic supplementary material:**

The online version of this article (doi:10.1186/s12913-016-1335-4) contains supplementary material, which is available to authorized users.

## Background

The diagnosis of cancer has an enormous impact on people’s lives. In additional to the threat on one’s physical health, cancer patients are confronted with psychosocial problems and care needs [1–13]. Timely and accurate detection of those psychosocial problems and care needs is of great importance to offer more patient-centered care, efficient referral and to prevent comorbid psychopathology [14–18].Simple quality of life (QOL) measurement and distress-screening are popular methods to explore people’s psychosocial well-being [9, 19–22]. In contrast, needs assessment is a strategy that focuses on identifying the unresolved concerns that patients are experiencing and determines if they desire further assistance throughout the continuum of care [23]. Indeed, not all patients experiencing distress or reduced QOL and need professional support from the care system [24]. Needs assessment can provide important input from the patients’ perspective and guide appropriate intervention in the multidisciplinary process of care. As a result of patient-report data, health care resources can be allocated in the most appropriate way. The use of needs assessment can therefore contribute to patient-centered quality cancer care [14, 25–27].

To our knowledge there are no validated Flemish needs assessment tools available. Therefore, this study will be dedicated to the validation of a needs assessment tool for use in Belgian research and clinical practice. To provide a good understanding of psychosocial healthcare needs, the content of a needs assessment tool should be comprehensive enough to benefit multidisciplinary stakeholders involved in cancer care i.e. medical specialists, nursing, psychologists, social welfare workers, general practitioners, health insurance agencies. In the search for an appropriate needs assessment tool, the following criteria were used: 1) the instrument should be generic across tumor type and staging, i.e. suitable in all cancer patients; 2) the assessment should encompass the bio-psychosocial impact of the disease and treatment on patients’ overall well-being i.e. physical, emotional, cognitive, social, relational, sexual and financial, their daily functioning and the potential resulting care needs; and, 3) the tool should have a proven psychometric robustness, demonstrating good reliability and validity, and be feasible for patients.

Several review studies describing needs assessment tools for adult cancer patients are available [28–30]. From the tools discussed 24 instruments are patient-reported outcomes (PRO) for adult patients with any type of cancer. These needs assessment tools and associated psychometric properties are presented in brief in Table 1 (and in full in Additional file 1).

**Table 1 Tab1:** Summary of needs assessment tools and psychometric properties

Instrument	Validity		Reliability		Responsiveness	Feasibility		
	Content Validity	Other types of validity	Internal consistency	Reproducibility		Time, Reading Level, Acceptability		
CaNDI	+	+	+	+	-	T: -	RL: +	A: -
CARES	+	+	+	+	-	T: +	RL: -	A: +
CARES-SF	+	+	+	+	+	T: +	RL: -	A: -
CCM	+	+	+	+	-	T: +	RL: +	A: +
CHOICEs	+	-	+	-	-	T: +	RL: -	A: +
Concerns checklist	+	+	-	-	-	T: -	RL: -	A: -
CNAT	+	+	+	-	-	T: -	RL: -	A: +
CNQ-SF	+	+	+	-	-	T: +	RL: +	A: +
CPILS	+	+	+	-	-	T: -	RL: -	A: -
CPNS	+	-	+	-	-	T: +	RL: -	A: +
CPNQ	+	+	+	+	-	T: +	RL: +	A: -
Distress management tool	+	-	-	-	-	T: -	RL: -	A: -
INM	+	-	+	-	-	T: -	RL: -	A: -
NEQ	+	+	+	+	-	T: -	RL: -	A: +
OCPC	+	-	-	-	-	T: -	RL: -	A: +
PINQ	+	+	+	-	+	T: -	RL: -	A: +
PNAS	+	-	+	-	-	T: -	RL: -	A: -
PNAT	+	+	+	+	-	T: +	RL: -	A: -
PNI	+	+	+	-	-	T: -	RL: +	A: -
Problem checklist	+	+	+	-	-	T: -	RL: -	A: +
SCNS	+	-	+	-	-	T: +	RL: +	A: +
SCNS-SF34	+	+	+	-	-	T: -	RL: +	A: -
SNST	+	-	-	-	-	T: -	RL: +	A: +
Symptoms and concerns checklist	+	+	+	+	-	T: +	RL: +	A: +

+ : evidence for psychometric property

- : no evidence for psychometric property or evidence not available

*Abbreviations*: CaNDI (Cancer Needs Distress Inventory), CARES (Cancer Rehabilitation Evaluation System), CARES-SF (Cancer Rehabilitation Evaluation System-Short Form), CCM (Cancer care monitor), CHOICEs assessment (Creating better health outcomes by improving communication about patients’ experiences assessment), CNAT (Comprehensive needs assessment tool in cancer), CNQ-SF (Cancer Needs Questionnaire Short Form), CPILS (Cancer Problems in Living Scale), CPNS (Cancer Patient Need Survey) CPNQ (Cancer Patient Need Questionnaire), Distress management tool, INM (Information Needs Measure), NEQ (Need Evaluation Questionnaire), OCPC (Oncology Clinic Patient Checklist), PINQ (Patient Information Need Questionnaire), PNAS (Psychosocial needs assessment survey), PNAT (Patient Needs Assessment Tool), PNI (Psychosocial Needs Inventory), Problem checklist, SCNS (Supportive Care Needs Survey), SCNS-SF34 (Supportive Care Needs Survey Short Form), SNST (Supportive Care Needs screening Tool), Symptoms and concerns checklist

Among other tools, the Cancer Rehabilitation Evaluation System (CARES) was positively evaluated [28–30]. The CARES is a QOL and needs assessment instrument, developed to provide an efficient way of gathering specific information about the day-to-day problems and rehabilitation needs of cancer patients. The instrument can be used for research or clinical objectives and has been applied across cancer type and stage [31–44]. The 139 items of the CARES are placed under 31 subscales and represented according to six summary scales, as shown in Table 2. A copy of the original CARES questionnaire and patient score profile can be found in Additional files 2 and 3.

**Table 2 Tab2:** CARES Summary scales and subscales

Summary scales (n items)	Subscales
Physical (26)	Ambulation Activities of daily living Recreational activities Weight loss Difficulty working Pain Clothing
Medical Interaction (11)	Problems obtaining info from medical team Difficulty communicating with medical team Control of medical team
Marital^a^ (18)	Communication with partner Affection with partner Interaction with partner Overprotection by partner Neglect of care by partner
Psychosocial (44)	Body image Psychological distress Cognitive problems Difficulty communicating with friends/relatives Friends/relatives difficulty interacting Anxiety in medical situations Worry Interaction with children^a^ At work concerns^a^
Sexual (8)	Sex interest Sexual dysfunction^a^
Miscellaneous (32)	Compliance Economic barriers Dating^a^ Chemotherapy-related problems^a^ Radiation-related problems^a^ Ostomy^a^ Prosthesis^a^ Miscellaneous items

^a^ Items may not apply to all patients

The psychometric robustness of the CARES and its earlier development versions (the Cancer Inventory of Problem Situations) are well documented [33, 34, 36, 45]. The results demonstrate that the CARES and its summary scales have excellent internal consistency (α = 0.87–0.94) and high test-retest correlations (*r* = 0.84–0.95). The instrument has moderate to high correlations with the Symptom Checklist-90 (SCL-90) [46], Dyadic Adjustment Scale (DAS) [47], Karnofsky Performance status Scale (KPS) [48, 49] and a visual analogue scale [50] for QOL before and after cancer, that were used to investigate concurrent validity. The content validity was supported with the results from post-administration interviews [35, 45].

Considering the CARES is reported as a valid and feasible tool that can be used for all cancer patients to assess a comprehensive range of bio-psychosocial aspects of well-being, this instrument was chosen to be translated and validated for further use in Flemish cancer care facilities and research.

The psychometric robustness of the Flemish CARES version will be tested thoroughly. We plan to evaluate the internal consistency of the CARES and its summary scales, the test-retest reliability will be considered, the construct validity will be explored, and the concurrent validity of the CARES and its summary scales will be checked with several comparative instruments. This paper describes the study protocol of this multi-stepped process.

## Methods

### Translation of the CARES

Belgium is a trilingual country with Dutch, French and German as official state languages. The Dutch language in Belgium, called Flemish, is slightly different from the Dutch language in the Netherlands in terms of vocabulary. Since current CARES translation is made for the Dutch-speaking part of Belgium, this paper refers to the Flemish CARES version only. We have no knowledge of a CARES translation appropriate for The Netherlands. However, there is a translation of the CARES-Short Form (CARES-SF) [51]. If one would like to use the full version of the CARES in The Netherlands, a revision of the translation would be needed.

The Flemish CARES version resulted from a forward-backward translation process with sworn translators and an expert group, following the guidelines for translating questionnaires described by Beaton et al. [52]. First, sworn translators translated the original US English CARES into Flemish. Two independent researchers revised the resulting texts for content fidelity and an expert group, comprised of professionals from the field of care management, oncology, primary care and psychology, agreed on the final Flemish version. The questionnaire was again translated back into English by sworn translators and the original CARES and English back-translation were compared by a native speaker, concluding the content of the questionnaire was maintained.

### Design of the study

A mix of qualitative and quantitative methods will be used for the validation study of the Flemish CARES.

Qualitative data collection, that will be used to evaluate *content validity* and *feasibility* of the instrument, will consist of conducting focus group discussions until data saturation is reached. We estimate that it will be necessary to arrange four or five focus group discussions with six to ten participants. The discussions will be facilitated with several key questions and transcribed afterwards for thematic content analysis. Further detailed description of this qualitative research activities will be part of another publication, since we prefer to focus on a detailed description of the quantitative research in this paper.

For the quantitative data collection, questionnaires containing the CARES and different complementary instruments (see further) will be used to evaluate *reliability, construct validity and concurrent validity.* This quantitative part of the validation study is described in further detail in this protocol.

### Sample size

There are no general criteria for the sample size in a validation study, but a sample size of at least 50–100 is generally recommended [53]. Sample sizes in the validation research of the original CARES varied for each psychometric quality (Table 3) [35]. Two large sample sizes of 479 and 1047 were used for the investigation of construct validity. Other aspects of reliability and validity were tested with sample sizes of 22 to 120 participants. Given the available time and resources, setting the goal to include 150 participants for this validation study of the Flemish CARES version is feasible. Considering the response rates of 40–60 % that are usually reached in the research domain of psycho-oncology, inviting at least 250 eligible patients is a conservative approach to guarantee the minimal amount of 150 participants.

**Table 3 Tab3:** Sample sizes validation research original CARES

Psychometric quality	Analysis	Sample size (N)
Test-retest reliability	Correlations between CARES summary scores	71 120
	Rating agreement	71 120
Construct validity	Factor analysis on all items	479
	Second-order factor analysis on 31 subscales	479 1047
Concurrent validity	Correlation between CARES and SCL-90	87
	Correlation between CARES and SCL-90, DAS, KPS and QOL visual analogue scale	120
Sensitivity	CARES compared to clinical interview	22
	CARES compared to a needs assessment interview	24 64
Content validity Acceptability to patients	Questions on relevance of CARES content, completion time, understandability and acceptability items.	22 64

*Abbreviations CARES* Cancer Rehabilitation Evaluation System, *SCL-90* Symptom Checklist-90, *DAS* Dyadic Adjustment Scale, *KPS* Karnofsky Performance status Scale

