### Study procedure

Eligible patients will be selected by the medical team according to the inclusion and exclusion criteria. Given the complexity of the clinical field and variable structures of the participating departments, two alternative procedures to invite patients to participate in the study will be used. On the basis of team organization and availability of time, the physician of the medical unit will choose to recruit patients with either the ‘face-to-face procedure’ or the ‘post procedure’. In the ‘face-to-face procedure’, a member of the medical team will explain the study briefly and invite the patient to participate. If the patient agrees to participate, he/she will immediately receive a study package with the informed consent form, a ‘what to do’-scheme, the first questionnaire and a stamped and addressed envelope to return the questionnaire. In the ‘post procedure’, eligible patients will be sent an identical study package by post, containing a short letter explaining the study, the informed consent form, a ‘what to do’-scheme, the first questionnaire and a stamped and addressed envelope to return the questionnaire. One week later participants have to fill in the second questionnaire, containing the CARES for test-retest reliability, and send it back in another stamped and addressed envelope provided. If the questionnaire is not sent back, the participants recruited via the ‘face-to-face procedures will be contacted by a team member and asked if they still want to participate and asked to return a completed questionnaire. Participants invited through post-procedure will be sent a reminder and second questionnaire package after 1 month. This study procedure is visualized in Fig. 1.

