## Discussion

To achieve good quality care it is important to provide it as efficiently as possible, and adapted to the individual needs of every patient. A stepped care approach according to patients’ level of need could serve to tailor care efficiently and appropriately, however this necessitates reliable and valid screening and assessment tools to support clinicians in the identification of psychosocial concerns and care needs of their patients. The current English CARES is such an instrument. This paper describes a comprehensive protocol for translating and validating a Flemish CARES version. This addresses a critical gap in current clinical screening, and adds a tool to assess and improve the delivery of patient-centered care.

Unique in this study is the use of a wide range of comparative instruments to examine the concurrent validity of the CARES. Many other validation studies use only a few dimensions, not reflecting the whole concept of the specific instrument [28, 29, 75]. In contrast, this study will include an instrument to examine concurrent validity almost for each summary scale and the CARES global score. While our study is set up to examine the psychometric quality of the Flemish CARES, an additional advantage is that the use of several concurrent instruments will provide us with a wealth of data. The use of the KPS, HADS, SSL, MMQ, EORTC QLQ-C30, DT, PL and the Care needs questionnaire of Pauwels et. al. provides data on psychological, social, marital and sexual wellbeing, QOL, distress and care needs of patients treated for cancer. These can be used to explore potential relationships between mutual care-domains and with socio-demographic and medical characteristics. The recruitment for this study has begun (March 2014) and will continue until the end of 2014 or until the desired sample size is reached.

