Thirdly, the questionnaire package composed with the CARES and several concurrent instruments asks for a time-investment of approximately an hour. This could present a burden to participants, resulting in discontinuation of participation. However, preliminary study results report approximately 58 % of the questionnaires distributed were returned completed. Eighty-four percent of the 153 participants who returned the first questionnaire also returned the second questionnaire completed.

Fourthly, the time between completing of the first and the second CARES survey could pose some problems. To examine test-retest reliability of an instrument the time period between two completions should be short enough to ensure that clinical change has not occurred, though long enough to prevent recall. While 1 or 2 weeks are recommended in literature [53], we ask participants to fill out the second questionnaire 1 week after the first. Preliminary results have shown some participants forget to fill in the second questionnaire or do not do so in a timely manner. They are reminded with a phone call by the researcher when de second questionnaire is not received in the recommended period of time. When data collection is completed, the time span between the two CARES-completions will be evaluated.

Fifthly, in earlier research the CARES was validated and used as a research tool for participants with various types of cancers, various cancer stages, at different phases of the care process, and often without age restrictions [31–44]. Because of the strict inclusion criteria we applied in our study, we have to state that the validation evidence from this study will not apply to patients above 60 years of age, and those with metastatic disease or in palliative care.”

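### The 250 invitations described as conservative are a best-case figure: they give an expected 150 participants only at the top of the quoted 40–60% response range

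*Protocol article*

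**What the plan says.** The Sample size section of the protocol article sets the target on grounds of time and resources: "setting the goal to include 150 participants for this validation study of the Flemish CARES version is feasible". It then works out how many patients to approach. The premise is "Considering the response rates of 40–60 % that are usually reached in the research domain of psycho-oncology", and the conclusion in the same sentence is that "inviting at least 250 eligible patients is a conservative approach to guarantee the minimal amount of 150 participants".

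Two places in the Discussion bear on this. The third limitation says that "preliminary study results report approximately 58 % of the questionnaires distributed were returned completed" and that "Eighty-four percent of the 153 participants who returned the first questionnaire also returned the second questionnaire completed". Earlier in the Discussion, recruitment is said to have begun in March 2014 and "will continue until the end of 2014 or until the desired sample size is reached".

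**The concern.** A conservative recruitment figure allows for the unfavourable end of the assumed response range. Here the number of invitations appears to come from the favourable end, in the very sentence that gives the range. The word *guarantee* adds a second difficulty: dividing a target by a response rate gives the number of invitations at which the target is the expected yield, and an expected yield is not assured.

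What is at stake is the stated basis for reaching 150. Someone who took the sentence at face value and budgeted for 250 invitations would, at the low end of the quoted range, end up one third short of the stated minimum (100 instead of 150).

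**Working it through.** **Inputs, all from the protocol article**
- Target: 150 participants (Sample size).
- Assumed response: 40% to 60% (Sample size).
- Planned invitations: at least 250 (Sample size).
- Preliminary return rate: about 58% of questionnaires distributed (Discussion, third limitation).
- First questionnaires returned: 153, of which 84% were followed by a completed second questionnaire (same place).

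**Step 1: reproduce the plan's figure.** Invitations = target / response rate. 150/0.60 = 250, an exact match. Neither the middle nor the bottom of the range gives it: 150/0.50 = 300 and 150/0.40 = 375.

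**Step 2: yield of 250 invitations, and invitations needed.** Expected participants = 250 × rate; invitations for an expected 150 = 150 / rate, rounded up.

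| Response rate | Expected from 250 | Invitations for an expected 150 |
|---|---|---|
| 40% | 100 | 375 |
| 50% | 125 | 300 |
| 58% | 145 | 259 |
| 60% | 150 | 250 |

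The 58% row assumes that the reported return rate applies per invitation (see the objection).

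**Step 3: does 250 guarantee 150 even at the best rate?** For illustration, take exactly 250 invitations and independent responses with one common probability. The exact binomial chance of at least 150 is then about 0.53 at 60%, 0.28 at 58%, 0.0009 at 50% and negligible at 40%. These describe a fixed 250, not the study, whose number of invitations is open-ended. They show only that 150 is an expectation at 60%, with roughly even odds of being met.

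**Step 4: what the preliminary figures imply.** If the 58% refers to first questionnaires, 153/0.58 ≈ 264 packages went out. Allowing for rounding of the 58%, the range is 153/0.585 ≈ 262 to 153/0.575 ≈ 266. The target was thus passed with somewhat more than 250 packages, at a return rate close to the top of the assumed range.

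**Step 5: test-retest pairs, for information.** 0.84 × 153 ≈ 129 pairs; for exactly 150 participants, 0.84 × 150 = 126.

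**The case against.** The best defence is that 250 was never a cap. The article says at least 250, and its stopping rule lets recruitment run until the sample size is reached or 2014 ends. The attained number therefore depends mainly on that rule. The target was also met, with 153 first questionnaires returned. At about 58%, the gap for exactly 250 invitations is only five participants. All of this stands, and it makes the point minor. It does not rescue the wording, because the sentence claims that the floor itself secures 150, and by the quoted range it does not.

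Three stronger readings are tempting and are not supported.

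- **That the study was at risk of failing its target.** A reader might infer this from the 100 expected at 40%. The end-of-2014 limit was a real constraint in principle, but the 153 returns settle the matter.
- **That the rate per invited patient must be below 58%.** In the face-to-face route, "If the patient agrees to participate, he/she will immediately receive a study package", so patients who refuse at that step never enter a denominator of distributed questionnaires. That would push the rate per invited patient down. But the Study procedure section also has non-responders in the post route receive a reminder with another questionnaire package after one month. If those repeat packages count as distributed, the rate per patient could be above 58%. The article gives neither the refusals nor the split between routes, so the direction is unknown.
- **That loss between questionnaires is an error in the sample size.** The target is 150 participants; nowhere does the article promise 150 test-retest pairs. It discloses the 84% openly. The resulting 126 to 129 pairs exceed the general recommendation of 50–100 and the samples of 71 and 120 listed in Table 3 for test-retest of the original instrument.

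**Conclusion.** The concern holds as a correction to the justification. The Sample size section labels a best-case number as conservative: 250 = 150/0.60 uses the top of its own 40–60% range. Over that range, 250 invitations are expected to yield 100 to 150 participants, and 150 is not assured even at 60%. The low-end calculation gives 375, which is 125 more than stated.

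The range of 100 to 150 rests only on figures in the article. The 145 at 58% carries the added assumption that returns per questionnaire distributed equal participation per invitation. Severity is minor: no analysis, threshold or attained sample size changes.

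**What to change.** In the Sample size section, remove *conservative* and *guarantee* and restate the calculation. Suggested wording: *At response rates of 40–60%, 250 invitations are expected to yield about 100 to 150 participants. To expect 150 participants, 375 invitations are needed at 40%, 300 at 50% and 259 at 58%. Inviting will continue beyond 250 as needed, within the recruitment period that ends when the target is reached or at the end of 2014.*

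If the 58% is cited there, say whether it is per questionnaire distributed or per patient invited, and label any equating of the two as an assumption. The expected number of test-retest pairs (about 126 for 150 participants at 84%) may be added for information.

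The cost is a change of wording. The target, design and analyses stay as they are.
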